## 4.3 Dose Escalation Principles

(1) Following the "3+3 principle", that is, three subjects were enrolled in each group, and the safety and tolerability of the first cycle were observed after administration. If no DLTS occurred, the trial proceeded to the next dose level according to the established dose-escalation protocol. If one DLT occurred, three more subjects were added at that dose level. When no new DLT occurred, the trial was continued at the next dose level. If ≥ 2 DLTS occurred, the dose level preceding that dose level was defined as MTD.

(2) The subjects with DLT were treated by the investigators according to the clinical diagnosis and treatment standards, and the dose could be delayed for no more than 2 weeks, the original dose could be maintained, or the dose level could be lowered to continue the next cycle. If no DLT occurred in the three patients enrolled in the first dose group during the observation period, the subsequent treatment was escalated to the second dose level.

(3) If more than one patient experienced DLT at the prespecified lowest dose, the lower dose was explored by the investigator.

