## 4.2 Dose Escalation Regimen

The dose-escalation scheme is designed based on a comprehensive evaluation of non-clinical in vitro pharmacodynamic data, existing clinical efficacy evidence and Safety profiles.

Arm A: Participants in this arm will complete the neoadjuvant therapy with irinotecan liposome (intravenous injection, once every two weeks for 1 month, dose increasing regimen: 37.6 mg/m2 and 56.5mg/m2) and epirubicin (intravesical instillation, once a week for 1 month, 50 mg).

Arm B: In the induction phase, the first three participants received a reduced dose of irinotecan liposomes (37.6 mg/m2, once every two weeks) in combination with standard intravesical EPI chemotherapy (50 mg, once a week) during the first cycle. If the combination was well tolerated, the irinotecan liposome dose was escalated to the full dose (56.5 mg/m2, once every two weeks) in the second cycle. The remaining three participants received the full dose of irinotecan liposomes (56.5 mg/m2, once every two weeks) along with standard EPI (50 mg, once a week) in both treatment cycles. Epirubicin was given at a fixed dose of 50 mg q1w for 4 cycles. In the maintenance phase, Epirubicin 50 mg q1m was intravesical instillation for a total of six cycles.

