## 6.5 Termination Criteria

The study may be prematurely terminated or temporarily suspended based on the following criteria:

(1) Identification of unexpected, significant, or unacceptable risks to study participants;

(2) Discovery of critical protocol flaws during trial execution.

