## 9.2 Diarrhea

Diarrhea caused by irinotecan liposome injection usually consists of both early-onset and late-onset diarrhea. Cholinergic action can result in early-onset diarrhea (occurring during or shortly after administration of the drug). It may be accompanied by rhinitis, increased salivation, miosis, tearing, diaphoresis, flushing, bradycardia, and hyperperistalsis that can cause abdominal cramps. If cholinergic syndrome occurs, atropine 0.25 to 1mg (total dose ≤1mg/ day) is recommended for treatment. Study participants who had acute cholinergic symptoms during previous treatment could receive atropine prophylactically until the next dose, at the investigator's discretion.

late-onset diarrhea (usually occurring after 24 hours after administration of irinotecan liposome injection, beginning with the first loose stool) may be of long duration and may result in dehydration, electrolyte disturbances, or infection, even fatal.

Once late-onset diarrhea occurs, it is recommended to give imodil treatment in time. Study participants were instructed to have imodium available and to start treatment if they had irregular or loose stools or more frequent bowel movements than previously reported. The imodil regimen was administered with an initial dose of 4mg, followed by 2mg every 2 hours until 12 hours after the study participants had stopped having diarrhea. In the evening, study participants could take Imodium 4mg every 4 hours. Continuous use of the above doses of imodil for more than 48 hours is not recommended because of the risk of paralytic ileus, nor is it recommended for less than 12 hours. Prophylactic administration of imodil is not recommended.

When diarrhea causes electrolyte disturbance and induces QTc interval prolongation, electrolyte supplementation is needed in time. When the underlying abnormality is recovered and the electrocardiogram is abnormal, the treatment can be continued with intensive monitoring, and the dose can be carefully adjusted.

If diarrhoea is present, it needs to be recorded at least to the hour.

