# 16. Quality Control and Quality Assurance

All investigators must be physicians trained in clinical trials and work under the supervision of senior professionals. Clinical wards must be inspected prior to the trial to ensure compliance with standardized requirements, including the availability of complete emergency equipment. It is recommended that specialized nursing staff administer investigational drugs to participants, with thorough documentation of medication administration to ensure participant compliance. All study sites must strictly adhere to the research protocol and maintain timely and accurate records.

Monitors shall follow standard operating procedures to oversee trial conduct, verifying that all data are recorded and reported accurately and completely. Electronic case report forms must be entered promptly and correctly, with consistency maintained between electronic records and source documentation to ensure protocol compliance.

In the event of a SAE, the study activities may be temporarily suspended if necessary. The trial site shall be subject to audits by the sponsor and drug regulatory authorities. Most critically, investigators and relevant personnel must provide the necessary access and time for monitoring and audit activities.

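### No pause is compulsory after a fatal or life-threatening event: the written next step in 4.3(1) can be three more participants at the same dose; separately, 12.4 and 14.3.1 give different adverse-event windows

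*Protocol*

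**What the plan says.** **Escalation rule (Protocol 4.3).** For each cohort of three, "the safety and tolerability of the first cycle were observed after administration". With no DLT the next level opens. With one, "If one DLT occurred, three more subjects were added at that dose level". With two or more, the preceding level becomes the MTD. Item (2) adds a condition for moving up: "If no DLT occurred in the three patients enrolled in the first dose group during the observation period". Item (3) lets the investigator explore a lower dose if more than one participant has a DLT at the lowest level.

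**Arm B schedule (4.2).** The first three participants receive 37.6 mg/m2 in cycle 1. For cycle 2: "If the combination was well tolerated, the irinotecan liposome dose was escalated to the full dose". Then: "The remaining three participants received the full dose of irinotecan liposomes (56.5 mg/m2, once every two weeks", in both cycles.

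**Suspension.** Section 6.5: "The study may be prematurely terminated or temporarily suspended based on the following criteria"; the criteria are unacceptable risk or a critical protocol flaw. Section 16: "In the event of a SAE, the study activities may be temporarily suspended if necessary".

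**Known hazard (9.2).** Late-onset diarrhoea after irinotecan liposome "may result in dehydration, electrolyte disturbances, or infection, even fatal".

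**Adverse-event windows.** Section 12.4 ends the safety follow-up period 7 days after the last dose and afterwards limits collection to SAEs considered drug-related. Section 14.3.1 sets the end of the safety follow-up period at 30 days after the last dose.

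**The concern.** The allocation rule counts DLTs. After the gravest event this trial could produce, its written instruction can be to expose more people, while the only provisions that would stop this are permissive. Whether anyone reviews the event before the next participant is dosed is therefore left to judgement on the day. The participants have cTa-cT1N0M0 disease, and the support that the protocol describes for this particular combination is preclinical (1.2). A related death in that setting should compel a review.

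The two adverse-event windows are a separate matter. Sites cannot follow both, and under 12.4 events between day 7 and day 30 that are not judged related could go unrecorded.

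**Working it through.** The plan states no figure on this point, so the check is to set the provisions side by side.

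**Step 1. What follows a single fatal or life-threatening first-cycle event?** The protocol does not define DLT. If the event counts as one and is the only DLT in the cohort, 4.3(1) adds three at that dose. If it did not count and no other DLT occurred, 4.3(1) would open the next level. Dosing continues either way.

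**Step 2. Does anything else compel a stop for other participants?**

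| Provision | Binding? | Holds the next participant's dose? |
|---|---|---|
| 6.5 termination or suspension | No, discretionary | Only if the power is used |
| 16 suspension after an SAE | No, discretionary | Only if the power is used |
| 14.5 immediate SAE report | Yes | No |
| 14.1.3 causality assessment | Yes | No |
| 17 revised consent after significant new information | Yes | No dosing hold stated |
| 6.3, and Table 1 in 9.1 for severe infusion reactions | Yes | No, affected participant only |

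No row is both binding and a hold at study level.

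**Step 3. Arm B.** The first exposures to 56.5 mg/m2 fall in cycle 2 of the first three participants. The tolerability condition in 4.2 governs that step, and so precedes those exposures. The sentence starting the remaining three at 56.5 mg/m2 carries no condition. Item 4.3(1) observes the first cycle, whereas 4.3(2) refers to an observation period that is not expressly limited to cycle 1. The first points to no check on the cycle 2 exposures; the second leaves room for one.

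**Step 4. Size.** 4.3(1) adds 3. Against the planned 6-9 per arm (section 5), 3/6 = 50% and 3/9 = 33%.

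**Step 5. Which branch would apply?** The documents give no event risk, so this is an illustration with assumed per-participant risks p, for a cohort of three and independent events. P(exactly one) = 3p(1-p)²; P(two or more) = 3p²(1-p) + p³.

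| Assumed p | Exactly one | Two or more |
|---|---|---|
| 1% | 2.9% | 0.03% |
| 2% | 5.8% | 0.12% |
| 5% | 13.5% | 0.7% |
| 10% | 24.3% | 2.8% |

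Counting these events alone, the single-event branch is by far the likelier one. Other DLTs in the same cohort could still bring the count to two.

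**Step 6. Windows.** 30 - 7 = 23 days of disagreement between 14.3.1 and 12.4, both counted from the last study-drug dose.

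**The case against.** The strongest reply is that nothing here is an error. A 3+3 rule that acts on the number of DLTs is conventional. Section 16 attaches a suspension power to any SAE, which is a lower trigger than death or threat to life, and 6.5 adds one for unacceptable risk. Immediate reporting and causality assessment are already compulsory. In a single-centre study of 12-18 participants, preferring a duty to a power may look like taste. Most of this stands, and it is why the hold is offered only as an improvement. What it does not answer is that no binding provision puts a review before the next dose.

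Four stronger readings are tempting, and the documents do not support them:

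- **That the trial cannot be stopped after a death.** It can, under 6.5 or 16.
- **That three is the most who could be exposed.** With no review ever required, nothing caps the number: if the added three have no new DLT, 4.3(1) moves to the next level. Nor do the documents support an expected number, since they give no event risk and the power to suspend may be used.
- **That the remaining three in Arm B are certain to start at full dose whatever happens in cycle 2.** The observation period in 4.3(2) may cover those exposures.
- **That the 23-day gap undermines the hold.** It barely bears on it. Both windows run from the last study drug, and 3.2 counts epirubicin as one. Arm B participants on protocol receive monthly epirubicin for six months, so even a 7-day window then ends well after irinotecan exposure. Section 12.4 also provides visits or calls after the last irinotecan liposome dose and continued collection of related SAEs.

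**Conclusion.** The point holds as a cheap safety improvement. When a related death or life-threatening event is the single first-cycle DLT in a cohort, the written next step is three more participants at that dose, and no provision makes a pause or review compulsory first. This rests on the event being counted as a DLT, which the protocol does not state. The Arm B gap is the likelier reading of 4.2 with 4.3(1), but it is not settled. The size claimed is the three that 4.3(1) adds next.

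The disagreement between 12.4 and 14.3.1 needs no such assumption: the same period is given two lengths, and one must be corrected.

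**What to change.** Add to 4.3(1), with cross-references in 6.5 and 16:

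> Any death or life-threatening event (14.2.1) not rated definitely unrelated (14.1.3), in either arm, from the first irinotecan liposome dose to 30 days after the last, suspends new enrolment, first doses, dose escalation and further irinotecan liposome infusions in ongoing participants until the investigators and sponsor have documented a review and reported it to the ethics committee. The 3+3 count then resumes unless the review decides to stop.

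Two details matter. The scale in 14.1.3 has no category for a possible relationship and passes straight from probably related to possibly unrelated, so the trigger should exempt only the definitely unrelated rating. Four of the five categories then trigger the hold. The hold must also cover ongoing participants, or a cohort-mate could receive the next infusion before the review.

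Separately, change the collection period in 12.4 from 7 to 30 days to match 14.3.1. Section 10 already records concomitant medication to 30 days, and the clinic or telephone contacts in 12.4 can serve for day 30.

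The cost is one sentence, two cross-references and a corrected period, by amendment, with no new committee. The downside is a short hold, including delayed infusions for ongoing participants, after a rare event.

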# 5. Sample Size

Both arms are expected to enroll 6-9 subjects each, with a total planned enrollment of 12-18 subjects.

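### Section 4.3(1) sets no minimum number treated for the MTD label, so 37.6 mg/m2 can be declared the MTD on three first-cycle observations

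*Protocol*

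**What the plan says.** Section 4.3(1) describes a 3+3 scheme: "three subjects were enrolled in each group, and the safety and tolerability of the first cycle were observed after administration". The next steps depend on the DLT count at the level:

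- No DLT: "If no DLTS occurred, the trial proceeded to the next dose level according to the established dose-escalation protocol".
- One DLT: "If one DLT occurred, three more subjects were added at that dose level". This is the only expansion in the rule.
- Two or more: "If ≥ 2 DLTS occurred, the dose level preceding that dose level was defined as MTD".

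Section 4.2 gives two irinotecan liposome levels for Arm A: "dose increasing regimen: 37.6 mg/m2 and 56.5mg/m2". Arm B uses the same two. There, "the first three participants received a reduced dose of irinotecan liposomes (37.6 mg/m2, once every two weeks") in cycle 1 and, if that was well tolerated, "the irinotecan liposome dose was escalated to the full dose (56.5 mg/m2, once every two weeks) in the second cycle". The other three Arm B participants have 56.5 mg/m2 in both cycles. Section 4.3(2) repeats the move to the second level after 0/3, and mentions keeping the original dose only for participants who had a DLT.

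On size, Section 5 states: "Both arms are expected to enroll 6-9 subjects each", 12-18 in total. Section 15.5.3 specifies a Clopper-Pearson 95% interval for the DLT rate.

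**The concern.** A 3+3 rule moves up on thin evidence because the next cohort supplies more. Naming an MTD is a different step, since it says that the named level itself is tolerable. Here that statement follows automatically from failure of the level above, and nothing requires a further look at the level being named. With two levels, failure at 56.5 mg/m2 leaves 37.6 mg/m2 as the MTD whatever number was treated there.

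The within-participant escalation in Section 4.2 adds to the problem. The regimen runs for a month with dosing every two weeks, but on the 0/3 path the first Arm B participants leave 37.6 mg/m2 after cycle 1. The label could then be read as covering a two-infusion course when only its first infusion was observed at that dose. What is at stake is the dose statement that the trial hands on. Which DLTs count toward escalation is a separate matter.

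**Working it through.** **The plan's own figure.** Section 5 gives 6-9 per arm: 2 × 6 = 12 and 2 × 9 = 18, which matches the stated total. The paths of a two-level 3+3 scheme that reach the second level need 3+3 = 6, 3+6 = 9, 6+3 = 9 or 6+6 = 12 per arm. The stated range covers 6 and 9. It does not cover 12, the path on which both levels are expanded.

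**Who supports the label.** On the path 0/3 at 37.6 mg/m2 followed by two or more DLTs at 56.5 mg/m2, Section 4.3(1) adds nobody at 37.6 mg/m2. Support is three participants, observed in the first cycle.

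**Precision, by the protocol's own method.** The upper 95% limit for 0/n is 1 − 0.025^(1/n).

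- 0/3: 1 − 0.025^(1/3) = 70.8%
- 0/6: 1 − 0.025^(1/6) = 45.9%
- 1/6 (0.975 quantile of a Beta(2, 5) distribution): 64.1%

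**How often 0/3 arises.** The protocol gives no DLT rate, so a range of assumed true rates p at 37.6 mg/m2 is shown. The formulas are:

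- P(0/3) = (1−p)³
- Chance that three further participants would show two or more DLTs = 3p²(1−p) + p³
- Chance that the level passes as written (0/3, or 1/3 then 0/3) = (1−p)³ + 3p(1−p)² × (1−p)³
- Chance that it passes if at most 1/6 is required = (1−p)³ × [1 − 3p²(1−p) − p³] + 3p(1−p)² × (1−p)³

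| p | 0/3 | Next three show ≥2 | Passes as written | Passes at ≤1/6 |
|---|---|---|---|---|
| 20% | 51.2% | 10.4% | 70.9% | 65.5% |
| 30% | 34.3% | 21.6% | 49.4% | 42.0% |
| 40% | 21.6% | 35.2% | 30.9% | 23.3% |
| 50% | 12.5% | 50.0% | 17.2% | 10.9% |

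At p = 40%, for example: 0.6³ = 0.216; 0.216 + 0.432 × 0.216 = 0.309; and 0.216 × 0.648 + 0.432 × 0.216 = 0.233. Of all passes as written, 0.216/0.309, about 70%, rest on three participants. Over the four rates the share is 69-73%. The 0/3 column is not the chance of a three-person MTD, which also needs 56.5 mg/m2 to fail.

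**Exposure in Arm B.** Dosing every two weeks for one month over two cycles implies one infusion per cycle. This is inferred, because cycle length is not defined. On the 0/3 path, participants who tolerated cycle 1 go to 56.5 mg/m2 in cycle 2 and the other three start there. Those with both infusions at 37.6 mg/m2 number 0 of 3. If one of the first three has a DLT and 37.6 mg/m2 is expanded, Section 4.2 does not state the cycle 2 dose of the added participants, so the count cannot be determined.

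**Room for six at 37.6 mg/m2.**

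| Treated at 37.6 | Treated at 56.5 when it fails | Total as written | Total with six at 37.6 |
|---|---|---|---|
| 3 | 3 | 6 | 9 |
| 3 | 6 | 9 | 12 |
| 6 | 3 | 9 | 9 |
| 6 | 6 | 12 | 12 |

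Six at 37.6 mg/m2 fits within nine per arm whenever 56.5 mg/m2 fails in its first three.

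**The case against.** The rule is complete for this case. Asking for six at the MTD is a common refinement, and leaving it out can be called a design choice. MTD appears only in Section 4.3(1). The objectives and the primary endpoint concern DLT incidence, and the planned exact interval would show how imprecise three participants are. The observation window is the first cycle, so a lack of cycle 2 data does not contradict the rule. Six participants also give modest protection: 1/6 has an upper limit of 64.1%, not far below 70.8%.

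Much of this stands and limits the point. The MTD should not be presented as a listed endpoint or as the trial's main conclusion, and the gain from six should be judged on 1/6 as well as on 0/6. But an exact interval reported beside the DLT rate does not qualify a label that the rule attaches automatically.

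A reader might infer two stronger claims. The first is that no Arm B participant who tolerates cycle 1 can ever have two infusions at 37.6 mg/m2. That holds only on the 0/3 path; on the expanded path the dose is unstated, and Section 4.2 does not say whether tolerance is judged per participant or per cohort. The second is that two-cycle tolerability would be wholly unknown. Someone who tolerates 37.6 and then 56.5 mg/m2 has had the higher exposure, which supports two infusions at 37.6 mg/m2 if toxicity does not fall with dose. The question stays open for those who fail in cycle 2.

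**Conclusion.** The point holds in conditional form. Followed exactly, Section 4.3(1) can label 37.6 mg/m2 the MTD on three first-cycle observations that are compatible with a DLT rate of up to 70.8%. On that path no Arm B participant has had both infusions at that level. The path is an ordinary one: even at a true DLT rate of 40%, 0/3 occurs about one time in five, and three more participants would then show two or more DLTs 35.2% of the time.

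This rests on three assumptions: escalation is run within each arm, there is one infusion per cycle, and the DLT rates shown are illustrative. If the arms are pooled, Arm A participants would count as well and the number could differ. The Arm B statement does not extend to Arm A, because Section 4.2 does not say whether the two levels there apply within or between participants.

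**What to change.** In Section 4.3(1), make the label conditional: a level is called the MTD only if six DLT-evaluable participants have been treated at it and at most one had a DLT, where the planned 6-9 per arm leaves room. If 56.5 mg/m2 fails in its first three, there is room (3+3+3 = 9). Where the condition is not met, for example when 56.5 mg/m2 fails only after six, do not use the term MTD. Report the level with its number evaluable, DLT count, exact interval, and a statement that only the first cycle was observed at it.

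Sections 4.2, 4.3 and 5 must also be reconciled on what course of treatment the declared dose covers and on whether the arms are pooled for escalation. How any added participants are dosed is for the sponsor to decide.

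The cost is protocol wording, plus either a more modest dose statement or up to three participants and one more observation period within the planned size.

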## 4.4 Treatment Period Follow-up

Arm A: routine blood test, liver and kidney function, coagulation function and adverse reactions were followed up every cycle after the first cycle of Irinotecan liposomal treatment. Pelvic and abdominal enhanced MRI and cystoscopy were performed after the second cycle of irinotecan liposomal treatment. The patients who achieved CR and PR were treated with TURBT combined with intravesical therapy after judged by two senior urologists. Patients with SD or PD received subsequent therapy at the investigator's discretion.

Arm B: Routine blood test, liver and kidney function, coagulation function and adverse reactions were followed up every cycle after the first cycle of Irinotecan liposomal treatment. Pelvic and abdominal enhanced MRI and cystoscopy were performed after combination treatment.

